## Abstract

**Background:**

Many randomized controlled trials have investigated the effects of exercise on the rehabilitation of patients with breast cancer. However, the exercise forms used in most previous studies were monotonous. Therefore, we designed a protocol to estimate the effects of combined exercise intervention using Internet and social media software on the rehabilitation of postoperative patients with BC.

**Methods/Design:**

This study protocol is a randomized control trial with an intervention time of 12 weeks. After completing baseline questionnaire and physical fitness tests, the participants are randomized to the study group or the control group. Procedure contents of exercise intervention in the study group include: via phone step-recording app, ask the individuals to complete the target number of steps within a specified period of exercise, four times per week; face-to-face remote video guidance of individuals on muscle training, three times per week; common knowledge of physical exercise BC rehabilitation will be pushed regularly by social media apps every day. The control group will receive normal treatment and rehabilitation according to daily specifications of the hospital. The primary outcome will be the quality of life. The secondary outcomes are physical fitness and social cognitive indicators.

**Discussion:**

This study is a clinical trial to estimate the effects of combined exercise intervention based on the Internet and social media software for postoperative patients with breast cancer (BC). If expected results are achieved in this study, measures and methods of BC rehabilitation will be enriched.

**Trial registration:**

Chinese Clinical Trial Register, ChiCTR-IPR-17012368. Registered on 14 August 2017.

**Electronic supplementary material:**

The online version of this article (10.1186/s13063-018-2857-3) contains supplementary material, which is available to authorized users.

## Background

Breast cancer (BC) is a type of malignant cancer that severely harms women’s health worldwide and is the most common cancer in women in both developed and developing countries. In developing countries, the incidence of breast cancer is rising due to increased life expectancy, the expansion of urbanization, and the adoption of a western lifestyle [1]. The most common manifestations in postoperative BC patients are mental fatigue, anxiety, and even depression [2]. The functions of the upper extremities may be affected, which also leads to limited physical activity. Long-term reduced physical activity will cause decreased adult bone mineral density and decreased muscle and cardiopneumatic endurance, which will severely affect emotions and quality of life (QOL) [3].

It has been demonstrated in modern medical studies, both domestic and abroad, as well as clinical practice that sport activities may improve muscle strength and cardiopneumatic endurance in BC patients during BC rehabilitation and further improve their emotions and QOL [3–9]. In addition, some studies have shown that resistance training has a certain effect on the improvement of postoperative complications of lymphedema [10–12]. Therefore, it has been recommended that both resistance training and aerobic exercise be included in the postoperative BC rehabilitation plan [3]. Qigong is one type of traditional Chinese exercise which is a combination of physical activity, breathing exercises, and psychological adjustment that has long been applied in health promotion and the treatment of various chronic diseases [13–16]. Theoretically, fitness Qigong may improve postoperative QOL, physical fitness, and psychological status of BC patients. With the universalization and extensive applications of the Internet, exercise intervention and guidance via phone social media apps and remote video to BC patients becomes possible. Currently, some related studies have been carried out [17–19], but most of the previous studies express the same problem that the means of exercise intervention is overly simple, which may impact the effect of the intervention.

Therefore, we have designed a combined exercise intervention protocol applying multiple Internet social media and plan to evaluate the effectiveness of the protocol by a clinical trial using a high-quality methodology: to conduct a randomized controlled trial (RCT) to estimate the effects of combined exercise intervention based on the Internet and social media software for postoperative patients with BC.

## Methods and design

### Study design

This study is a RCT with an intervention time of 12 weeks. Trial participants were recruited starting in August 2017 and the data will be analyzed after the sample size is achieved according to the study design. The flow chart of the study design is shown in Fig. 1. Apart from the time and contents of the designed exercise plan being different between the study group and the control group, relative regulations of the hospital at other times are followed to ensure regular work performance in the hospital and ensure that the treatment of BC patients is not affected in the hospital. All participants will provide informed consent forms before entering the study.

**Fig. 1 Fig1:**
[figure not shown]
The flow chart of the trial design

### Participants and recruitment

Individuals who meet the inclusion criteria will be briefly introduced to this study and informed about the benefits as well as possible risks by the clinician. The participants will then be required to fill in consent forms and are free to withdraw from the study at any time without any specific reason, penalty, or loss of benefits.

### Inclusion criteria

Patients with BC phases I–III, who have finished postoperative radiotherapy/chemotherapy within four months to two years will be included.

### Exclusion criteria

Individuals who meet any of the following criteria will be excluded: (1) those with communication or language barriers and inability to complete the questionnaire; (2) those with metastasis, severe deterioration of conditions, or severe mental disorders; (3) those with a history of acute attempted suicide; (4) those with cognitive organic brain lesions and dementia; (5) those who cannot perform exercises of medium exertion and above; and (6) those who cannot use independently or with help social media app (WeChat official account), free-of-charge commercial smartphone apps, and remote video. Patients who meet one or more of the above criteria will be excluded from the study.

### Recruitment strategies

Participants will be recruited from the Department of Breast Surgery, the Second Hospital of Shandong University, Jinan, Shandong. Recruitment is mainly through the doctors’ recommendations, patients publicizing the trial, and the distribution of leaflets. Patients interested in this trial will first be evaluated by physicians. If they meet the criteria and decide to participate, they will be asked to sign the informed consent. They will then be included in the trial for randomization.

### Blinding

After completing the baseline questionnaire and physical fitness tests, the participants will be enrolled and a computer-generated random list generated by SPSS 16.0 will be used for randomization. The random number list is kept strictly confidential by the Data Coordination Committee (DCC) staff. Eligible patients will be randomized to the experimental group or the control group at a 1:1 ratio. The group numbers will be provided in envelopes made from carbonless paper. The envelopes will be kept by a study administrator who will not directly participate in the recruitment or follow-up of any participant and the group numbers will be subsequently disclosed. Different people will enroll participants and assign participants to interventions.

The division results are kept by the study designer until the end of the study to ensure allocation concealment, which means the allocation is bound to both the result evaluator and the data analyzer. The participants and the treatment provider will be instructed not to disclose the allocation to the result evaluator.

### Control group

Participants who have been randomized into the control group will receive normal treatment and examination according to the daily specifications of the hospital. The rehabilitation plan will also be performed according to the regular requirements and postoperative BC rehabilitation-related health education will be provided.

### Intervention group

Basic contents of intervention in the study group include cardiopneumatic endurance training, muscle training, conventional fitness exercises, and postoperative rehabilitation knowledge which pushed combined interventions: (1) cardiopneumatic endurance training: to be performed four times per week, determine the strength of the exercise via rate of perceived exertion (RPE), ask the individuals to complete the target number of steps within the specified time and record the number of steps via a phone step-recording app; (2) muscle training, fitness Qigong exercises: muscle training includes muscle strength, muscle endurance, and muscle function training while fitness Qigong exercise is scheduled after completion of muscle training, practicing certain Qigong Baduanjin fitness routines. Face-to-face remote video guidance on physical exercise rehabilitation is performed three times per week for 30 min each time, including a 5-min warm-up, 20 min of muscle training, and 5 min of relaxation. The primary content of muscle training is endurance training in the first month, strength training in the second month, and muscle function training in the third month. Traditional fitness exercise is scheduled after warming up and relaxing exercises and may include one or more routines each time; (3) postoperative BC rehabilitation knowledge: common knowledge of physical exercise BC rehabilitation pushed regularly by social media apps every day as well as knowledge of simple physical exercise rehabilitation and psychological adjustment relative to BC survivors.

Physical exercise rehabilitation training is performed under the guidance of the participants’ professional physiotherapists. The measures of exercise intervention will be gradually advanced and the strength of exercise will be gradually increased. The side effects and severe adverse events will be recorded and reported to the study designer by physiotherapists; the study designer will then determine further measures to take. In this case, other sports-related exercise interventions will stop, while treatment by medication will continue. If necessary, training will be discontinued according to the reports from the therapists and the consultation results from the BC specialists. We call the roll through every video guide, endurance training, and weekly group meeting to improve adherence to intervention protocols. There are no concomitant or prohibited interventions during this trial.

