### Measurements

The primary outcome of the trial will be the MOS 36-item Short Form Health Survey mental component summary scale (SF-36 MCS). The secondary outcomes are other sub-items of the MOS 36-item Short Form Health Survey physical component summary scale (other sub items of SF36) [20, 21], PROMIS, physical fitness, and social cognitive theory. Measurements will be conducted in the same place and by the same tester for both the study group and control group strictly adhering to the precautions and operational rules, to ensure that the measurements are scientific and precise.

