### Data collection and management

To ensure the accuracy of outcome assessments and data collection, all of the physicians, nurses, and research assistants will attend a training workshop before the start of the trial. All attendees will be provided with a protocol and standard operation procedures and will discuss the topics they may feel confused about until everyone is totally clear about the procedures. We do not have plans to promote participant retention and complete follow-up.

After screening and signing of informed consent and end-of-study measurements, the SF-36, physical fitness, and social cognitive theory will be carefully recorded. Monitoring will be performed by personnel independent of the investigators and the sponsor and will consist of checking all informed consent forms and completeness of all data and source data verification of patients. Data are collected and recorded on a standard report form; when the visit is completed, all the recorded data will be entered into the web-based data system by the double-entry method. All errors will need to be corrected by crossing out, with the researcher’s signature and date. Any participant may quit the study at any time for any reason. If any patients want to quit, clinicians will ask whether they agree to finish the follow-up according to the study schedule. All patients who quit and are lost to follow-up will be recorded. If our study fails to recruit 50% of patients within six months, we will stop the study. The process will be independent from investigators and the sponsor.

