### Ethical approval and dissemination

This study follows the principles of the Declaration of Helsinki (Version Edinburgh 2000). Before participating in this research, every potential participant should be informed of the detailed study information, while participants can ask questions by phone, e-mail, and face to face. Only patients who sign the informed consent form will be included. This study has been approved by the Ethics Committee of the Second Hospital of Shandong University (KYLL-2017(KJ)P-0003). Personal information about potential and enrolled participants will be collected and stored separately from medical records and will be only accessible for the assessors who contact the participants for data assessment. In case of an unexpected serious adverse event (e.g. life-threatening event or permanent damage) over the course of the study, we will report the serious adverse event to the local Ethics Committee. The Ethics Committee and the study team will then decide in accordance, in the best interests of the patient, if the study procedures will be continued or terminated. The results of this study will be disseminated by presenting at international conferences and publication in peer-reviewed journals. Participants will learn about the results of the study.

The principal investigator is responsible for publication of the results of this study in whole or in part. Neither the complete nor any part of the results of the study carried out under this protocol, nor any of the information provided by the sponsor for the purposes of performing the study, will be published or passed on to any third party without the consent of the study sponsor. The study designer will have access to the final trial dataset. Any investigator involved with this study cannot access the trial data. Data sharing statement is as follows: no later than three years after the collection of the one-year post-randomization interviews, we will deliver a completely deidentified dataset to an appropriate data archive for sharing purposes.

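### The only stated route for recording side effects runs through the exercise arm's physiotherapists, so event counts would have no comparable control rate

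*Protocol article*

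**What the plan says.** In the protocol article, the Intervention group section gives the recording route: "The side effects and severe adverse events will be recorded and reported to the study designer by physiotherapists". The same paragraph says what these physiotherapists do: "Physical exercise rehabilitation training is performed under the guidance of the participants’ professional physiotherapists". What follows a report is a decision by the study designer and, where needed, a halt to exercise. Contact in this arm is frequent: "Face-to-face remote video guidance on physical exercise rehabilitation is performed three times per week for 30 min each time", with attendance also checked at endurance training and at a weekly group meeting.

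The Control group section says: "Participants who have been randomized into the control group will receive normal treatment and examination according to the daily specifications of the hospital". It adds routine rehabilitation and health education, and says nothing about recording events.

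The Data collection and management section states: "After screening and signing of informed consent and end-of-study measurements, the SF-36, physical fitness, and social cognitive theory will be carefully recorded". Adverse events are not in that list. The Measurements section names the SF-36 mental component summary as primary; the secondary outcomes are the rest of the SF-36 together with "PROMIS, physical fitness, and social cognitive theory". None is a harm outcome.

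The Ethical approval and dissemination section opens its safety provision with "In case of an unexpected serious adverse event (e.g. life-threatening event or permanent damage) over the course of the study" and says that such an event is reported to the local Ethics Committee. This is not restricted to one arm.

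**The concern.** A recording route is fixed, and it sits with the staff who deliver one arm's treatment. Nothing equivalent is described for the other arm. If the text is followed, a sore shoulder, a swollen arm or a fall in an exercise participant has a ready path into the trial record. The same event in a control has none unless it is serious and unexpected.

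Such events also occur without exercise. The Background section itself mentions impaired upper-extremity function and lymphedema after breast cancer surgery. Exercise-arm counts therefore need a control rate to be interpretable, and as described they would not have a comparable one. A reader who set the two arms side by side would see an excess that partly or wholly reflects closer observation. The people doing the recording also know the allocation. What is at stake is the trial's account of harm, not its primary result.

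**Working it through.** The plan states no figure on harms, so there is nothing to reproduce. The check compares the provisions by arm and then illustrates the consequence.

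**1. Provisions by arm**

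| Item | Exercise arm | Control arm |
|---|---|---|
| Named recorder of side effects | Physiotherapists (Intervention group) | None stated (Control group) |
| Scheduled trial contact during the 12 weeks | Video sessions, endurance training, weekly meeting | None stated |
| Events in the list of recorded data | Not listed (Data collection and management) | Not listed |
| Unexpected serious events to the Ethics Committee | Yes | Yes, but no recorder or way of asking is named |

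The video sessions alone give 3 per week × 12 weeks = 36 scheduled contacts per exercise participant. These are training sessions. The text describes attendance checks at them, not event questioning. They are 36 opportunities for an event to be noticed or mentioned, not 36 event assessments.

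**2. Effect of unequal capture**

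Inputs from the article: 60 enrolled (Sample size) and "Eligible patients will be randomized to the experimental group or the control group at a 1:1 ratio" (Blinding), so 60 / 2 = 30 per arm.

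Assumptions, because the documents give no rates: the same true 12-week event rate p in both arms, every event captured in the exercise arm, and a share c of events captured in controls.

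Expected recorded events: exercise 30 × p; control 30 × p × c.

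False excess in the exercise arm = p − p × c = p × (1 − c).

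| p | Exercise events | Excess, c = 0 | Excess, c = 0.25 | Excess, c = 0.5 | Excess, c = 1 |
|---|---|---|---|---|---|
| 10% | 3 | 10 points (3 v 0) | 7.5 points (3 v 0.75) | 5 points (3 v 1.5) | 0 |
| 20% | 6 | 20 points (6 v 0) | 15 points (6 v 1.5) | 10 points (6 v 3) | 0 |
| 30% | 9 | 30 points (9 v 0) | 22.5 points (9 v 2.25) | 15 points (9 v 4.5) | 0 |

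The excess vanishes only when capture is equal. Under these assumptions it always counts against the exercise arm.

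**The case against.** The strongest reply is that this is a condensed article. It says that physiotherapists record events; it does not say that nobody else does. A reader might infer that control-arm recording is absent from the trial altogether. The documents do not support that: the full protocol, the SPIRIT schedule in Fig. 2 and Additional file 1 are not shown, and any of them could list a safety assessment for both arms. That limits the point to the visible text. It does not remove it, because the article goes beyond silence: it states a route and places it in one arm.

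Second, the sentence reads as an operational rule for managing people who are exercising, and no between-arm harm analysis is planned. Both are fair. The point therefore concerns what the counts could be used for; it does not identify an error in a stated analysis.

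Third, controls are not without coverage. Unexpected serious events in either arm go to the Ethics Committee, and PROMIS pain and physical function are planned outcomes for the trial as a whole. A reader might infer that the trial will hold no harm-related information on controls; that would be too strong. These provisions still give no counts of side effects or non-serious events, and no equal detection of serious ones. Nor does the text say who delivers the controls' routine rehabilitation, so it cannot be claimed that they never meet a physiotherapist. It shows only that no trial recording is described there.

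Finally, the small sample limits what either arm's count can say about rare harms. That would remain true with identical recording in both arms, so it is no argument for this point.

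**Conclusion.** The point holds for the text at hand. The only stated route for side effects and non-serious events passes through the exercise arm's physiotherapists. For controls nothing is stated beyond the reporting of unexpected serious adverse events. Followed as written, exercise-arm counts would lack a comparable control rate, and any between-arm comparison of harm would be biased against the intervention.

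The size cannot be established from the documents. The illustrated false excess of 5 to 30 percentage points rests on assumed true rates of 10% to 30%, equal in both arms, full capture in the exercise arm, and control capture between none and one half. Incomplete recording by the physiotherapists would make it smaller.

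The change is worth making because it is cheap and the defect concerns how harm will be read. The SF-36 mental component comparison is not affected. If Fig. 2 or Additional file 1 already provides a common safety assessment, the text need only say so.

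**What to change.** Add one identical, self-completed adverse-event page to the end-of-study questionnaires in both arms. It should ask about a fixed list over the past 12 weeks, for example arm swelling, falls, musculoskeletal injury and hospitalisation. Participants should complete it after the fitness tests, and the tester should not see it. This matters because the Blinding section keeps the outcome assessor unaware of allocation: if the tester asked about injuries in person, exercise participation could easily be disclosed before tester-scored measures were taken.

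State that any between-arm comparison of harm uses this page alone. Report physiotherapist-recorded events separately, labelled as exercise-arm-only data. Leave the Ethics Committee reporting of unexpected serious events as it is.

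The cost is one extra page at an existing visit, plus its data entry. The downside is recall error over 12 weeks. It may differ somewhat between arms, because participants know their allocation and those whose events were discussed during sessions may remember them better. That imbalance should be much smaller than the one created by recording through one arm's therapists.
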